### **Blinding**

No one will be blinded during this selection and allocation process in this study.

### **Quantitative component**

#### ***Study Population***

The study population will be married adolescent girls (MAGs) aged 15-19 years, their husbands, and community members aged 35-59 years.

#### ***Inclusion and exclusion criteria for clusters***

Any village with around 500 households or 35 MAGs will be considered as eligible to be included in this study.

#### ***Inclusion and exclusion criteria for individual participants***

##### Inclusion criteria

Criteria for inclusion of the MAGs in the study will be: i) adolescent girls aged 15-19 years; and ii) currently married and living with husband; and iii) both the girl and her husband have no intention of migrating out within the next 15 months. The husbands of the selected adolescent girls will also be included in the study. Community members aged 35-59 years will also be considered eligible for participating in the study.

##### Exclusion criteria

MAGs who are physically or mentally unstable to participate in the intervention and to respond to the interview questions will be excluded from the study. Any couple having plans to migrate out during the next one and a half years will not be included in this study.

#### ***Survey tools***

Three separate questionnaires will be developed to interview the married adolescent girls, their husbands, and the community members. The MAGs will be asked about their socio-economic and demographic characteristics, intrinsic, instrumental and collective agency, FP, first conception, unwanted pregnancy, birth interval, intimate partner violence (IPV), etc. In each of the SRHR domains studied, we will explore adolescent girls' knowledge, attitudes and practices with a focus on communication, negotiation, consent, choice and decision-making. Husbands of the MAGs will be asked about their knowledge and attitudes regarding SRHR relevant to them and to the MAGs, while the community members will be asked about social norms regarding SRHR of MAGs. The questionnaires will be developed in English and then translated into Bengali. The Bengali version of the questionnaires will be pre-tested, piloted and finalized. The English version of the questionnaires will be updated following the final Bengali questionnaire.

#### ***Data collection and management***

Data will be collected at baseline and endline through face-to-face interviews conducted by gender-matched interviewers upon receiving consent from the study participants. The data will be recorded using Tablets. An offline-based survey software will be developed for the purpose. Interviews will be conducted in private in a location convenient for the participants.

A survey team of six female and six male data collectors, two supervisors, one programmer and one survey coordinator will be employed in the survey. The survey team will be thoroughly trained not only in survey methods, the questionnaire, use of tablets and field procedures, but also in gender and rights, empowerment, gender-based violence, and ethics of conducting research on sensitive issues. The total training including the piloting will take around 12 days. The training will be participatory in nature.

### ***Survey data quality monitoring***

A strong data quality monitoring system will be in place. The supervisor will observe the quality of the interviews, keep notes and discuss problems during daily review sessions. The interviewers will cross-check each other's interviews randomly and provide feedback to the interviewers. The survey coordinator will randomly choose interviewers for spot checks. The data collected will be uploaded on a designated server at the end of each business day, which will allow the researchers to instantly review the data from the server. Further, a software-based data checking routine will be developed which will allow identifying inconsistencies in the data within a short period of time. A researcher will analyse the data on a weekly basis to identify any inconsistencies in the data and provide feedback to the survey team. Correction will be performed following standard procedure. Five percent of the study participants will be revisited by the supervisors and the coordinator for administering a short questionnaire as part of quality check. In addition, the researchers will visit the field on a regular basis, observe interviews, cross-check interviews, and provide feedback.

### **Qualitative Component**

This component will basically help us to compliment the quantitative component. If change happens as a result of the intervention, the qualitative study will provide insight into how change happens through empowerment of MAGs and social norm change. If change does not take place, it would help us understand what went wrong.

### ***Study population, sampling, recruitment in the cohort,***

The qualitative study will cover two intervention clusters. Data will be collected through Key Informant Interviews (KIIs), In-depth Interviews (IDIs), and Focus Group Discussion (FGDs). While KIIs and FGDs will provide data on social norms and general practices around SRHR of MAGs, IDIs will give us access to in-depth data on individual perceptions, practices and experiences.

We will conduct **KIIs** with mothers-in-law (MiLs) of the MAGs, Non-government Organization (NGO) staff implementing SRHR programmes in the study area, Community Health Workers (CHWs), village doctors / traditional healers /drug sellers. We propose to conduct KIIs with MiLs of MAGs since they are likely to be knowledgeable about the SRHR of the MAGs. NGO staff implementing SRHR programmes addressing SRHR due to their work experiences and interpersonal skills — make them credible and knowledgeable source of information for this research. We assume that MAGs may seek support and services for different SRHR issues from the traditional healers, village doctors/drug sellers, and NGO workers, making them important source of information.

We will conduct **IDIs** with the MAGs and their spouses. Criteria for inclusion of the respected respondents for IDIs are given below:

#### ***a) Married Adolescent Girls***

Criteria for inclusion in this cohort to be females: i) aged 15-19 years; ii) currently married and living with husband; and iii) currently none of the spouses are planning to migrate out during the next 15 months.

#### ***b) Spouses of MAGs***

This category includes spouses of the MAGs who have been interviewed in-depth.

The **FGDs** will be conducted separately with MAGs, their spouses and elderly women and influential community members.

Each KII, IDI, and FGD will take around one and a half hours. All interviews will be digitally recorded with consent of the respondents. We will collect three rounds of qualitative data throughout the study period. Table 1 describes the methods, participants, procedure, and tentative sample size.

**Table 1: Qualitative methods and participants**

| Methods                                                                                              | Participants                                                                                                                                       | Purpose                                                                                                                                                                               | Baseline                              | Endline                                        |
|------------------------------------------------------------------------------------------------------|----------------------------------------------------------------------------------------------------------------------------------------------------|---------------------------------------------------------------------------------------------------------------------------------------------------------------------------------------|---------------------------------------|------------------------------------------------|
| Method 1: Key Informant Interview (KII)                                                       |                                                                                                                                                    |                                                                                                                                                                                       |                                       |                                                |
| KII with mothers-in-law of MAGs, NGO staff, CHWs, village doctor/ traditional healers/ drug sellers. | 2.1. MiLs of MAGs

2.2. NGO staff

2.3. Government CHWs (e.g., FWV) 2.5.

2.4. Village doctors/drug sellers/ traditional healers | This method will generate information on empowerment, FP, child bearing including first conception, and DV of MAGs and social norms around these.                                     | 6                                     | 6                                              |
| Method 1: In-depth Interviews                                                                 |                                                                                                                                                    |                                                                                                                                                                                       |                                       |                                                |
| In-depth interviews with MAGs and their spouses                                                      | 1.1. MAGs aged 15-19

1.2. Spouse of MAGs aged 15-19                                                                                         | This method will generate information on knowledge, attitudes and practices regarding SRHR of MAGs' with a focus on empowerment and consent and choice and social norms around these. | 16 MAGs and

16 spouses of MAGs | No. of MAGs and spouses retained in the cohort |
| Method 3: Focus Group Discussion (FGD)                                                        |                                                                                                                                                    |                                                                                                                                                                                       |                                       |                                                |

|                                                                                                     |  |                                                                                                                                                                                       |                                                                                                          |                                                                                                          |
|-----------------------------------------------------------------------------------------------------|--|---------------------------------------------------------------------------------------------------------------------------------------------------------------------------------------|----------------------------------------------------------------------------------------------------------|----------------------------------------------------------------------------------------------------------|
| FGD with MAGs, their spouses, and elderly women and influential community members aged 35-59 years. |  | This method will generate information on knowledge, attitudes and practices regarding SRHR of MAGs' with a focus on empowerment and consent and choice and social norms around these. | 2 with MAGs;
2 with spouses of MAGs;
2 with elderly women;
2 with influential community members | 2 with MAGs;
2 with spouses of MAGs;
2 with elderly women;
2 with influential community members |
| Total                                                                                               |  |                                                                                                                                                                                       | 46                                                                                                       | 46 (max)                                                                                                 |

### ***Qualitative data collection tools, data collection and management***

The qualitative data collectors will have Masters degree in anthropology or any social science discipline. They will receive an 8-day training on gender, rights, empowerment, SRHR, communication, negotiation, decision-making, social norms, qualitative research methods, and research ethics. Interviewers will be gender matched with the informants. The end line will follow the same strategy enabling us to assess changes over time in the cohort of group members and in the community over time.

### **Sample Size Calculation and Outcome (Primary and Secondary) Variable(s)**

Clearly mention your assumptions. List the power and precision desired. Describe the optimal conditions to attain the sample size. Justify the sample size that is deemed sufficient to achieve the specific aims.

The sample size for the survey of MAGs was calculated based on the primary outcomes "ability of a MAG to achieve own choice regarding: (1) FP use; (2) conception; and (3) SRH service uptake". Considering a cluster size of 22 married adolescent girls and their husband, and assuming a 50% prevalence rate of ability of a MAG to achieve own choice in SRH issues among this group (as unknown), 15% effect size, an Intra-Cluster Correlation of 0.05, 5% significance level and 80% power we required 16 clusters per arm making the total number of clusters 32. Considering a 10% non-response rate at baseline, 20% refusal rate among MAGs interviewed at baseline to participate in the intervention, and another 15% drop out rate at endline among the MAGs participated in the intervention, the group size increased to 35 and total sample size increased to 1,120 MAGs. As these considerations provided us with the maximum sample size, this current sample size will allow us to measure the changes in all other secondary outcomes of the study.

The husband of the selected MAGs will also be included in the study to measure the secondary outcomes related to their knowledge and attitudes regarding SRHR relevant to them and the MAGs.

To assess social norm change we focused on social norms around the MAGs' consent and choice in SRH. We will assess this change surveying adult community members aged 35-59 years. Since the prevalence of positive social norms around consent and choice in SRH issues is unknown among this population we assumed it as 50%. Considering a 15% effect size, 5% significance level, 80% power and 5% non-response rate, we required 540 community members (270 females and 270 males) from 32 clusters. Dividing the numbers by number of clusters and then rounding up the total sample size increased to 576 (nine females and nine males from each cluster).

The qualitative sample size includes 6 KIIs, 32 IDIs and 8 FGDs at baseline and endline.

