### **Cluster formation and randomization,**

The villages from Rajbari Sadar upazila will be treated as clusters or the primary sampling units in this study. The list of villages and the number of households in each village will be obtained from the upazila statistics office. Any village/cluster with approximately 500 or more households will be considered eligible to be included in the study for allowing an adequate number of MAGs. Three teams, each consisting of two members, will visit each of the eligible villages, talk to local people, check which could be selected as study clusters and which could be potential buffers. All the teams will then finalize the list of eligible villages after ensuring sufficient buffer zone.

We will then randomly select 32 clusters/villages from the list of eligible villages. The selected 32 clusters will be subsequently assigned randomly to either the intervention or control group in a 1:1 ratio. The randomization process will be carried out by an independent statistician from icddr,b who will not be involved in the designing the study, recruiting the study participants, implementing the intervention or analysing the data.

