### **Abortion and post-abortion service uptake and help seeking by physically and/or sexually abused MAGs**

If any MAG reports having an induced abortion/MR, she will be asked about venue of the service received, provider and the method of abortion. The MAGs with an abortion will be asked about post-abortion care. The MAGs who report experiencing any physical and/or sexual intimate partner violence will be asked about their help seeking. The results will be presented in frequencies and percentages.

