Intention-to-treat (ITT) analysis will be used during assessing the impact of the intervention. Thus, all the MAGs enrolled at baseline and could be successfully interviewed at endline will be included in the analysis irrespective of their actual level of participation in the intervention activities. The information on participation of study participants in the intervention activities will come from the programme monitoring data and will also be used in the models. The impact of the intervention on primary and secondary outcomes will be assessed using risk ratios/regression coefficients derived from binary/linear regression analyses for measuring change in outcomes in the intervention arms relative to change in the control arm. Significance level will be set at  $p < .05$  for all analyses. The data will be analysed using STATA 16.

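### The sample-size paragraph says the trial is large enough for all other secondary outcomes, but this does not follow for outcome 10 (service uptake), which is measured only in girls reporting an abortion or violence

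*Protocol*

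**What the plan says.** The protocol's sample-size section bases the number of girls on "ability of a MAG to achieve own choice regarding: (1) FP use; (2) conception; and (3) SRH service uptake". Its inputs are: "Considering a cluster size of 22 married adolescent girls and their husband"; "assuming a 50% prevalence rate of ability of a MAG to achieve own choice in SRH issues among this group (as unknown"); and "15% effect size, an Intra-Cluster Correlation of 0.05, 5% significance level and 80% power we required 16 clusters per arm". It then concludes, of the remaining outcomes: "As these considerations provided us with the maximum sample size, this current sample size will allow us to measure the changes in all other secondary". No separate calculation is given for any other outcome measured in the girls.

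Table 2 lists one service-uptake outcome, secondary outcome 10. It covers abortion and post-abortion care, and help seeking after violence. The measurement section restricts its questions:

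- Venue, provider and method are asked if a girl reports an induced abortion or MR. "The MAGs with an abortion will be asked about post-abortion care".
- Help seeking is asked of girls who report physical and/or sexual intimate partner violence.

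That section plans frequencies and percentages for this outcome. The quantitative analysis section, however, makes no exception for it: "The impact of the intervention on primary and secondary outcomes will be assessed using risk ratios/regression coefficients", with significance set at p<.05 for all analyses.

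The hypothesis predicts a significant improvement that includes SRH service uptake, and primary objective 2 names the same domain. The current primary outcome does not include it. It is agency in decisions on FP use, timing of first conception and number of children.

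**The concern.** An assumed rate of 50% gives the largest sample size only under two conditions: the absolute difference is held at 15 points, and every sampled girl supplies a value. It gives no protection to an outcome observed in only some of the girls, because the loss there comes from the denominator and not from the variance at a given rate. Outcome 10 is such an outcome by its own definition.

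SRH service uptake is one of three domains in the hypothesis and in primary objective 2. A reader of the sample-size section would take it that the trial can measure change in that domain about as well as in the others. The design does not supply that assurance. The protocol also points two ways on analysis, with description in one section and testing in another.

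**Working it through.** **Inputs.** From the sample-size section: 22 girls per village, 16 villages per arm, 50% control rate, 15% effect, ICC 0.05, 5% significance and 80% power. Allocation is 1:1 (cluster formation and randomization section). Sidedness is not stated, so two-sided is assumed. The effect is read as absolute, 50% vs 65%. A relative reading, 50% vs 57.5%, would need 65 villages per arm, so it is not what was used.

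**Step 1: the plan's own figure.**

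- n per arm without clustering, pooled-variance z: [1.96·√(2·0.575·0.425) + 0.8416·√(0.25 + 0.2275)]² / 0.15² = 169.3, rounded up to 170.
- Design effect: 1 + (22 − 1)·0.05 = 2.05.
- Villages per arm: 170·2.05/22 = 15.84, rounded up to 16. The stated figure reproduces.
- Effective n at 16 villages: 352/2.05 = 171.7 per arm. Power is 81% (z) or 79% (t, 30 df), so there is almost no slack.

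**Step 2: a subset outcome.** Let f be the share of girls who are asked the question. The protocol gives no value for f, so it is an assumption. Then m = 22f girls per village contribute, the design effect is 1 + (m − 1)·0.05, and n_eff = 16m divided by that design effect. With unpooled variance, power = Φ(0.15/√(0.4775/n_eff) − 1.96). For example, at f = 30%: m = 6.6, design effect 1.28, n_eff = 105.6/1.28 = 82.5, and 0.15/0.0761 − 1.96 = 0.01, so power is about 50%.

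| Assumed f | Girls per village | n_eff per arm | Power, z | Power, t (30 df) |
|---|---|---|---|---|
| 5% | 1.1 | 17.5 | 14–15% | 14% |
| 10% | 2.2 | 33.2 | 23–24% | 23% |
| 20% | 4.4 | 60.2 | 38–39% | 37% |
| 30% | 6.6 | 82.5 | about 50% | 48% |
| 50% | 11.0 | 117.3 | 64–65% | 62% |
| 70% | 15.4 | 143.3 | 73–74% | 71% |
| 100% | 22.0 | 171.7 | 81% | 79% |

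The z column spans pooled and unpooled variance.

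**Step 3: sensitivity.**

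- *More girls analysed.* The intention-to-treat text keeps girls who decline the intervention, so only baseline non-response and endline dropout reduce the number: 35·0.90·0.85 = 26.8 per village. Power at 50% vs 65% is then about 16% at f = 5%, 26–28% at 10%, 54–56% at 30% and 68–70% at 50%.
- *Lower baseline rate.* With 10% vs 25% and 22 girls per village, power is 21–22% at f = 5%, 71–73% at 30%, 79–82% at 40% and 85–87% at 50%. Power can therefore exceed 80% for a subset outcome, but only with a large subset and a rate the protocol does not assume.

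**Step 4: two denominators.** Girls with an abortion or MR and girls with partner violence are different groups. Each part of outcome 10 has its own f, so the table has to be read once for each part.

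**The case against.** Four points can be made for the plan.

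*The 80% is for another construct.* The sample-size section powers the ability to achieve one's own choice regarding service uptake, not uptake itself. No section restricts that choice measure to girls with an abortion or violence, and the section on knowledge, attitudes and practices says the girls in general will be asked about SRH service uptake. This stands. A reader might infer that the protocol claims 80% power for outcome 10, and the text does not say so. What remains is the sentence on all other secondary outcomes, which does cover outcome 10. In addition, no listed outcome scores the choice construct for service uptake.

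*Description is already planned.* Frequencies and percentages are specified for this outcome, and the regression sentence is general. This stands in part. It makes the remedy small, but the general sentence and the p<.05 rule contain no exception, so the two sections need reconciling.

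*The power figures are not the protocol's.* This stands. A reader might infer that power for outcome 10 is a known 14–65%. That range needs an assumed share of 5–50%, a 50% baseline rate and ICC 0.05 within the subset, and the documents support none of these for this outcome. It also treats two denominators as one.

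*Weak power for one of 21 secondary outcomes is ordinary.* It is, and a rule for interpreting it may sit in an analysis plan that is not at hand. A reader might infer that a non-significant result would be reported as no effect, but nothing in the protocol says that. The point concerns only a printed statement of adequacy that does not follow from its premise.

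**Conclusion.** The sample-size arithmetic is sound, and nothing here affects the number of villages or girls. What fails is the extension of that calculation to all other secondary outcomes. For outcome 10, fewer than 22 girls per village contribute unless every girl reports the qualifying event. On the plan's own 50% vs 65% and ICC 0.05, power then falls below the 80% for which the size was fixed, apart from the slight slack between 15.84 and 16 villages. That conclusion needs no outside prevalence.

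The size of the shortfall is conditional. It runs from severe (about 14–15% power at a 5% share) to moderate (62–65% at a 50% share), is slightly less with 26.8 girls per village, and may vanish if the baseline rate is low and the share is about 40% or more. No single figure should be quoted as the power of outcome 10.

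**What to change.** 1. In the sample-size section, limit the adequacy sentence to binary outcomes measured in all girls, for a 15-point difference with ICC up to 0.05.
2. State there that outcome 10 is not powered and is descriptive. Report the abortion/MR part and the violence part separately, each on its own denominator, with cluster-adjusted confidence intervals.
3. In the quantitative analysis section, exempt outcome 10 from the p<.05 testing so that it agrees with the frequencies and percentages planned in the measurement section.
4. Align the endpoints named in the sample-size section with the current primary outcome, which omits service uptake and includes number of children.
5. Qualify the hypothesis wording on SRH service uptake accordingly.

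The cost is protocol wording. No extra participants, villages or data are needed. The price is a more modest claim for one outcome domain.

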For the community survey, separate cross-sectional samples will be drawn and interviewed at baseline and endline. We will obtain lists of eligible community members (females and males), aged 35-59 years from household enumeration. Nine females and nine males will be randomly selected from each cluster for inclusion in the surveys making the total in each round 576.

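### The community sample of 540 (576) rests on an undisclosed design effect, and on the binary planning outcome the stated change-versus-change comparison does not reach 80% power at any ICC from 0 to 0.05

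*Protocol*

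**What the plan says.** The sample size section sizes two surveys.

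- **Girls.** The inputs are all listed: "Considering a cluster size of 22 married adolescent girls and their husband", 50% prevalence, a 15% effect size, and "an Intra-Cluster Correlation of 0.05, 5% significance level and 80% power we required 16 clusters per arm".
- **Community members.** The prevalence of positive norms "is unknown among this population we assumed it as 50" per cent. Then: "Considering a 15% effect size, 5% significance level, 80% power and 5% non-response rate, we required 540 community members", split as "270 females and 270 males) from 32 clusters". After rounding, "the total sample size increased to 576 (nine females and nine males from each cluster". No ICC or design effect is given for this survey.

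Two other places define what the sample has to support. Under household enumeration, sampling and recruitment, "separate cross-sectional samples will be drawn and interviewed at baseline and endline". Under quantitative data analyses, the impact on primary and secondary outcomes is estimated "for measuring change in outcomes in the intervention arms relative to change in the control arm". The sample size section itself gives the purpose of the community survey as assessing change in social norms.

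**The concern.** A reader who puts the listed inputs into the usual formula does not get 540. The calculation must contain a clustering allowance that is not stated, and it cannot be the ICC used one paragraph earlier.

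The figure also corresponds to a single comparison of two proportions. A difference of changes between two independent cross-sections carries baseline sampling error as well as endline sampling error, so the same number of interviews gives less power.

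Outcomes 17 to 21 come from this sample alone. Outcome 22 (social norms) and the objective on norm change also use the girls' survey. If the protocol's 80% is taken at face value, a null result in the community survey would be read as stronger evidence of no effect than the design supports.

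**Working it through.** **Inputs from the protocol.** 50% prevalence; 15% effect, read as 50% to 65%; 5% significance; 80% power; 5% non-response; 32 villages, 16 per arm; 18 people per village per round. ICC 0.05 is stated for the girls only.

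**Assumptions.** Two-sided test; a range of community ICCs from 0 to 0.05; village-level correlation between rounds, r, from 0 to 1.

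**1. Check the reading on the girls' survey.** With p̄ = 0.575,

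n per arm = [1.96√(2p̄(1−p̄)) + 0.84√(0.25 + 0.2275)]² / 0.15² = 169.3.

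Design effect = 1 + 21 × 0.05 = 2.05. Clusters per arm = 169.3 × 2.05 / 22 = 15.8, so 16. The protocol's figure is reproduced, which supports this reading of the inputs.

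**2. Same formula, community inputs.**

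| Formula | n per arm | Total after 5% non-response (2n/0.95) |
|---|---|---|
| Unpooled | 166.6 | 351 |
| Pooled | 169.3 | 356 (358 with 170 per arm) |
| Continuity-corrected | 182.4 | 384 (386 with 183 per arm) |

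Other readings also miss 540: one-sided gives 283, 90% power gives 478 (506 with continuity correction), and a relative effect of 50% to 57.5% gives 1,459.

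**3. What 540 implies.** Expected respondents are 540 × 0.95 = 513.

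- Design effect: 513 / (2 × 169.3) = 1.51; unpooled 1.54; continuity-corrected 1.41.
- Respondents per village: 513 / 32 = 16.0.
- Implied ICC: 0.51 / 15.0 = 0.034; with continuity correction 0.41 / 15.0 = 0.027. So about 0.03.

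**4. Power of 576, endline only.** n per arm = 576 × 0.95 / 2 = 273.6, or 17.1 per village. DEFF = 1 + 16.1 × ICC. SE = √(0.4775 × DEFF / 273.6). Power = Φ(0.15/SE − 1.96).

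At ICC 0.05: DEFF 1.805, SE 0.0561, power 76% (73% with t on 30 df).

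**5. Power of 576, change versus change.** Three of the four arm-by-round means have variance term 0.25 and one has 0.2275, which sum to 0.9775.

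- ICC 0: SE = √(0.9775 / 273.6) = 0.0598; power = Φ(2.51 − 1.96) = 71%.
- ICC 0.05, r = 0: SE = √(0.9775 × 1.805 / 273.6) = 0.0803; power 46%.
- ICC 0.05, r = 1: the shared village effect removes 0.977 × 0.05 × 17.1 / 273.6 = 0.00305 from the variance of 0.00645; SE 0.0583; power 73%.

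**6. Endline adjusted for the village's baseline mean.** The village means in the two rounds correlate at R = r × ICC × 17.1 / DEFF, and the SE is multiplied by √(1 − R²). At ICC 0.05 and r = 1: R = 0.855 / 1.805 = 0.474, SE 0.0494, power 86%.

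| ICC | Endline only | Change versus change, r = 0 to 1 | Endline adjusted for baseline mean, r = 0 to 1 |
|---|---|---|---|
| 0 | 95% | 71% | 95% |
| 0.03 | 84% | 54% to 72% | 84% to 88% |
| 0.04 | 80% | 50% to 73% | 80% to 87% |
| 0.05 | 76% | 46% to 73% | 76% to 86% |

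Even with full response from all 576, the change comparison at ICC 0.05 and r = 1 reaches only 75%.

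**7. Size needed at ICC 0.05, endline only.** With 32 villages fixed, a larger sample raises the cluster size and so the design effect. Required respondents per village solve m / (1 + 0.05(m − 1)) = 170 / 16 = 10.6, giving m = 21.5. Invited: 21.5 / 0.95 = 22.7, so 23 × 32 = 736.

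**The case against.** **The ICC of 0.05 belongs to another population and outcome.** This stands. The protocol states it for girls aged 15 to 19 and their own choices, not for norms held by adults aged 35 to 59. A reader might infer that 576 is underpowered at endline at the trial's ICC. The document does not support that: no community ICC is given, and at the value near 0.03 that 540 implies, endline power is about 84%. It falls below 80% only from about 0.04.

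**540 shows that clustering was allowed for.** This also stands. A reader might infer that clustering was ignored, but 170 × 2 × 1.5 / 0.95 = 537, close to 540. The fault is an undisclosed input that differs from the neighbouring one.

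**The outcomes are summative scores, so binary power is only a planning figure.** This stands as a limit on the size of the point. If 50% to 65% is read as a 0.385 SD shift across a median cut of a normal score, endline power at a score ICC of 0.05 is Φ(0.385√(273.6 / (2 × 1.805)) − 1.96) = 92%. The protocol also divides scores into tertiles, and it sized the survey on a proportion. The power it states is for that proportion.

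**The change sentence is general, and the study outcomes section says outcomes are measured after the intervention.** The exact model may properly be left to a statistical analysis plan. But the protocol itself states the change contrast, the separate samples and the 80%, and these do not fit together on the planning outcome.

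**A correlation of 0 between rounds is pessimistic for the same villages.** That is fair, and the full range is shown for this reason. At r = 1 the figure is still below 80%.

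**Conclusion.** The point holds in three parts of different strength.

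1. **540 does not follow from its listed inputs.** They give about 351 to 358 (384 to 386 with continuity correction). An unstated design effect of about 1.4 to 1.5 is needed. This rests on arithmetic alone, with the reading of the inputs confirmed on the girls' survey.
2. **Endline-only power for 576 cannot be judged from the protocol.** It is 84%, 80% or 76% at ICC 0.03, 0.04 or 0.05, the last being an assumption carried over from the girls' survey.
3. **The stated change comparison is below 80% on the binary planning outcome at every ICC from 0 to 0.05.** It is 71% at ICC 0 and 46% to 73% at 0.05. The spread reflects the assumed correlation between rounds, which the protocol does not give.

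A reader might go further and conclude that the norm-change objective as a whole is underpowered. The documents do not support this, because outcome 22 is also measured among the girls. All affected outcomes are secondary.

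**What to change.** - State the ICC or design effect behind 540. If it differs from the 0.05 used for the girls, give the reason.
- Name the comparison the community sample is meant to power, and restate the power of 576 for it on the binary planning outcome. For an endline comparison: about 84% at ICC 0.03, 80% at 0.04 and 76% at 0.05 for a 15-point difference.
- Analyse the endline community sample with the village's baseline mean as covariate, in place of change versus change. This gives about 84% to 88% at ICC 0.03 and 76% to 86% at 0.05, against 54% to 72% and 46% to 73% for the change comparison. At ICC 0.05 with little correlation between rounds it may still fall short of 80%.

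The cost is a few sentences and one covariate, with no added interviews. The drawback is that the stated power becomes less favourable.
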